### Ethical Considerations

The study will be conducted according to the guidelines of the Declaration of Helsinki. The study was approved by The Central Denmark Region Committees on Health Research Ethics (record 1-10-72-277-21, 1-10-72-80-22, and 1-10-72-142-22).

Written informed consent will be obtained from parents and adolescents (≥15 years) whereas children and adolescents (<15 years) will only give oral consent.

Children and adolescents will be compensated with a gift card (value 150 DKK [US $21.13]) for the first time participating in the interoception study. No other compensation will be provided.

## Results

Recruitment of participants began in June 2022. Substudy 1 is finalized and expected to be published in 2025. Recruitment for substudies 2 and 3 is ongoing. By November 2024, 45 children and 24 adolescents have been included. Due to a skewed distribution in referrals, with a predominance of referrals on children, we continue to include children and adolescents until we have reached 30 adolescents. Inclusion is expected to be completed by January 2025 and data collection in March 2025.

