**Methods:**

Children (8-12 years), adolescents (13-17 years) with FAPDs, and their respective parents will be included for 10 weeks for ICBT. First, detailed trajectories of effect are examined through a randomized single-case design study involving 6 children and 6 adolescents (substudy 1). Following this, an open-ended explorative pilot study with 30 children and 30 adolescents explores potential illness-related cognitive biases and interoceptive accuracy before and after treatment (substudy 2). Finally, spanning across these 2 substudies, including all parents from substudies 1 and 2, we will assess parental distress and illness worries before and after treatment, and how these factors impact the treatment adherence and outcomes of the child or adolescent (substudy 3).

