## Methods

### Study Design

The study includes 2 recruitment phases. The first phase concerns a single case experimental design (SCED) study (substudy 1) with a total of 12 patients (6 children and 6 adolescents, respectively). The second phase concerns an open pilot study on cognitive biases and interoceptive accuracy (substudy 2) with a total of 60 patients (30 children and 30 adolescents, respectively).

Consequently, a total of 72 children and adolescents, along with a corresponding number of parents, will undergo ICBT for FAPDs throughout the entire study. Parental distress and illness worries will be assessed before, during, and after the treatment in all included parents (substudy 3; Figure 1).

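### The stated 72 patients and 30 + 30 split in substudy 2 no longer match the counts and recruitment rule in Results, and the revised target cannot be identified

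*Protocol article*

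**What the plan says.** Study Design describes the single-case study (substudy 1) as one "with a total of 12 patients (6 children and 6 adolescents, respectively") and the open pilot (substudy 2) as one "with a total of 60 patients (30 children and 30 adolescents, respectively"). It concludes that "a total of 72 children and adolescents, along with a corresponding number of parents, will undergo ICBT for FAPDs throughout the entire study". The Methods part of the Abstract repeats the substudy 2 figure: "an open-ended explorative pilot study with 30 children and 30 adolescents".

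Results gives a different picture: "By November 2024, 45 children and 24 adolescents have been included". It states the reason, "Due to a skewed distribution in referrals, with a predominance of referrals on children", and then the rule now in force: "we continue to include children and adolescents until we have reached 30 adolescents". No upper limit on children is given. The same paragraph says that substudy 1 is finished and that substudies 2 and 3 are still recruiting. It does not say which substudies the 45 and 24 cover, or which ones the 30 refers to.

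Sample Sizes gives 60 patients and 100 controls as the requirement for the cognitive bias outcome, and at least 51 and 51 for interoception. It takes the substudy 3 sample to be all parents from substudies 1 and 2. Data Analyses compares patients with healthy controls by t tests or nonparametric tests, and uses negative binomial and linear mixed models in substudy 3. No age term is mentioned in either place.

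**The concern.** The article gives two accounts of its own sample. One is a fixed, equally split 72. The other is a recruitment rule that leaves one age group open-ended, with a count for that group already above its share of 72. A reader cannot tell how many patients are now intended, or whether 30 or 36 adolescents will be treated in all.

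The age mix matters for the analysis. Children and adolescents receive different programmes, and their parents receive 10 and 5 modules respectively (Design and Content of Treatment). Averages over a pooled sample therefore depend on the proportion of children. In substudy 2, patients are compared with a separate healthy control group. The Discussion calls the 96 controls for the cognitive bias task age-matched, but their age split is not given. If the patient group drifts towards children because of referral patterns, an unadjusted comparison has no protection against a difference in age mix between the two groups.

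**Working it through.** **The plan's own figure.** Substudy 1 is 6 + 6 = 12, substudy 2 is 30 + 30 = 60, and 12 + 60 = 72. This reproduces the stated total. Per age group, 6 + 30 = 36; the 36 + 36 is not printed but follows by addition.

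**Inputs from Results.** 45 children and 24 adolescents by November 2024; both groups stay open until 30 adolescents; no cap on children.

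**Possible readings.** The 45 + 24 may or may not include the 6 + 6 single-case patients, and so may the 30. One of the four combinations rules itself out. If the counts left out substudy 1 but the 30 included it, adolescents would already be at 24 + 6 = 30 and recruitment would have stopped. Three remain. The figures below are minimums: they assume that the 30 is reached and that no child was enrolled after November 2024.

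| Reading | Substudy 2 (children + adolescents) | Overall (children + adolescents) |
|---|---|---|
| Counts and the 30 both include substudy 1 | (45 − 6) + (30 − 6) = 39 + 24 = 63 | 45 + 30 = 75 |
| Counts include substudy 1; the 30 is substudy 2 only | 39 + 30 = 69 | 45 + 36 = 81 |
| Counts and the 30 are both substudy 2 only | 45 + 30 = 75 | 51 + 36 = 87 |
| Stated plan | 30 + 30 = 60 | 36 + 36 = 72 |

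On every reading, children exceed both the 30 planned for substudy 2 (39 or 45) and the 36 implied overall (45 or 51). The total exceeds 72 by at least 3, 9 or 15.

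**Age mix at these minimums.** The proportion of children in substudy 2 is 39/63 = 62%, 39/69 = 57% or 45/75 = 60%. Overall it is 45/75 = 60%, 45/81 = 56% or 51/87 = 59%. The design has 50%.

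**If referrals kept the 45:24 ratio (an assumption).** Children at 30 counted adolescents would be 45 × 30/24 ≈ 56. The overall total would then be about 56 + 30 = 86 on the first reading and 56 + 30 + 12 = 98 on the third. On the second, the counted adolescents must reach 36, so children would be 45 × 36/24 = 67.5 and the total about 104.

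**Power for the pooled patient-control comparison** (two-sample t test, d = 0.5, two-sided α = .05; the article does not state sidedness):

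- Cognitive bias: 60 v 100 as planned, 86.1%. With the 96 controls actually tested: 63 v 96, 86.5%; 69 v 96, 88.3%; 75 v 96, 89.7%.
- Interoception, with the 60 controls named in the measures section: 60 v 60, 77.5%; 63 v 60, 78.5%; 75 v 60, 81.8%.

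Power does not fall on any reading.

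**The case against.** The strongest defence is that this is a disclosed deviation and not a miscalculation. The sum to 72 is right. Results is a dated status report that gives the change, its cause and the new rule, and Study Setting and Recruitment separately reports the slow adolescent referrals and the wider catchment area. The study is largely exploratory, and age adjustment could sit in an analysis plan that is not shown.

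Most of that stands and limits the point, but it does not remove it. The recruitment rule in Results is current and looks forward, and it appears in the same article as a total of 72 that the rule cannot produce. Disclosing skewed referrals does not tell the reader what the revised target is or what the counts cover.

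Three stronger inferences are tempting and are not supported:

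- **That adolescents in substudy 2 fall short, at 24 instead of 30.** This holds only on the first of the three readings. The figure of 30 equals the substudy 2 target, which makes the other readings at least as natural. The matching claim of adolescent intervals about 12% wider (√(30/24) = 1.118) has the same condition, and the article sets no precision target for adolescents alone.
- **That the powered comparison is weakened.** The power figures show otherwise. The minimum of 63 patients also meets both the 60 and the 51 in Sample Sizes.
- **That the patient-control comparison is biased.** The controls' age split is not given, and nothing in the article says that task performance differs by age. The before-after contrasts are within person, so age mix can shift their average but does not confound them.

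**Conclusion.** The point holds as an unreconciled sample size. The total of 72 and the equal age split in the Abstract and Study Design cannot be what the recruitment rule delivers, whichever way the counts are read. The excess is at least 3 to 15 patients, both overall and in substudy 2, and children make up at least 57% to 62% of substudy 2 at the November 2024 child count. These figures assume that recruitment runs until the 30 is reached. The proportion of children rises further if more of them enrolled, because no cap is stated.

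The consequence is an undefined target and a patient group whose age mix is set by referrals. It is not lost power. Whether the age mix distorts the comparison with controls cannot be determined from the article, and that is a reason to account for age in the analysis rather than evidence of bias.

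**What to change.** In the Abstract and Study Design, keep the original plan on record and add the revised target for each substudy and age group. State whether the 45 + 24 and the 30 adolescents include the single-case patients, and whether enrolment of children is capped. Correct the total of 72 to match. Leave the 60 in Sample Sizes unchanged, because it is a power requirement and not an enrolment count.

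In Data Analyses, replace the unadjusted patient-control tests in substudy 2 with a comparison adjusted for age or stratified by age group. Include age group in the pooled substudy 3 models and report results by age group. If an unpublished analysis plan already does this, a sentence saying so is enough.

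The cost is some rewording, slightly more analysis work with a variable already collected, and a stated design that looks less balanced. No extra patients are needed.

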## Discussion

### Principal Findings

With this study, we aim to explore previously sparsely investigated areas of ICBT for children and adolescents with FAPDs related to both child or adolescent and parental factors. This includes examining the detailed trajectory of effect, the presence of and potential changes in cognitive biases, and interoceptive inaccuracy after treatment, as well as investigating the potential role of parental distress, illness worries, and behavior as effect moderators.

Previous studies have demonstrated the effectiveness of Swedish ICBT programs in reducing abdominal symptoms and improving the quality of life in children and adolescents with FAPDs. Mediation analyses have shown that positive changes in symptom-specific avoidance behavior and fear mediate the treatment effects [17,18,27,29]. However, the detailed trajectory of treatment effects—specifically when and how possible changes occur during treatment for individual patients—remains unknown, and this will be investigated in substudy 1. This research could provide new insights into the mechanisms of change underlying treatment effects and could be clinically valuable for both therapists and patients.

To the best of our knowledge, this study is one of the first to assess cognitive biases and the ability to sense and interpret signals from the body (ie, interoception) in this patient group in comparison with healthy controls as well as to explore potential changes in these factors after treatment with CBT. Both factors are suggested to play a vital role in the predictive processing model, explaining the pathophysiology of FAPDs [11]. However, so far, they have mainly been studied in adults with various functional disorders [40,68-69,75-78]. By uncovering more knowledge about these factors, the results can potentially be used to further refine already established treatments. For example, this could involve adding biofeedback to train interoceptive accuracy or enhancing exposure exercises addressing specific cognitive biases that lead to fearful responses to gastro-related sensations and avoidance behavior.

Parental worries and anxious behaviors toward the child or adolescent’s symptoms can impact the overall well-being of the child or adolescent. These factors are suggested to be part of the complex pathophysiology of FAPDs [9,20,21,48] and are therefore important to investigate further. Parental emotional distress has been found to negatively moderate the effect of ICBT for adolescents with chronic pain [79,80], whereby high levels of parental emotional distress lead to less improvement in disability for the adolescent. However, it is currently unknown how the level of parental distress impacts the effects of the ICBT programs for young patients with FAPDs [29,81]. A specific type of parental emotional distress is health anxiety by proxy, which is a recently described clinical phenomenon characterized by parents’ excessive and distressing worries and rumination about their child’s health, often involving fears of serious diseases being overlooked by medical professionals [82,83]. This fear may lead to frequent medical visits and investigations of the child [84]. In this study, we will use the newly developed HAPYS questionnaire [46,47] to assess parental health anxiety by proxy. To our knowledge, this is the first systematic examination of this specific type of parental emotional distress in parents of children and adolescents with FAPDs. Such type of parental anxiety may especially lead to symptom-related protective and monitoring behaviors, which are suggested to play a crucial role in the development, maintenance, and even aggravation of the child’s FAPD and related health care visits [48-50]. The Swedish ICBT has been shown to effectively reduce such maladaptive parental behavior in both children and adolescents [28,29]. Still, the impact of parental emotional distress, particularly illness worries and related behavioral responses, on the effect of ICBT in children is less well-investigated [85] and no studies have yet been conducted specifically in relation to adolescents. This is why, in this study, we will explore parental distress, illness worries, and behaviors before and after ICBT and examine how these factors impact treatment adherence and treatment effects in both children and adolescents. By uncovering more knowledge about these parental factors, we aim to gain a better understanding of family dynamics and identify potentially important parental characteristics to focus on during treatment, thereby further improving its effectiveness.

The study has some limitations. In substudy 1, the generalizability of SCED study results has traditionally been questioned due to the low number of participants. However, our study adheres to guidelines that include multiple data points across different phases, randomization of the length of the baseline phase, and replication across several participants, thereby optimizing generalizability. Furthermore, participants are expected to answer daily questions for an extended period, which could induce some fatigue in responding and potentially affect reliability. Still, the inclusion of several close data points increases precision in analyses and helps buffer against occasional data loss. In addition, the setup was tested on 4 prestudy patients, who reported that the daily questionnaire was easy and quick to answer.

In substudy 2, we use the BY-GIS task, which is newly developed and has not been previously tested in patients. However, the task is developed based on well-known paradigms and previous tests, and it has already been tested in a sample of 96 healthy age-matched controls with good usability [38]. The interoception HRD measures participants’ ability to sense their pulse, which is not directly related to gut sensations but falls within the broader perspective of interoception. However, studies in adults suggest altered interoceptive accuracy across different diagnoses of functional disorders and chronic pain, which indicates that there may be a general hypersensitivity to inner sensations in this patient group as well [86]. Since this study is one of the first to investigate interoceptive accuracy in children and adolescents with FAPDs, we believe it is still valuable to use this well-known and widely used interoception measure.

Substudy 3 is an open pilot trial without a control group for comparison which means conclusions regarding the clinical effect of the treatment should be interpreted with caution. However, the substudy is explorative and primarily aims to investigate new and additional modifiable treatment targets on a parental level.

### Conclusion

In conclusion, this study is expected to provide new and important information about the process of the effect of ICBT, increase our understanding of modifiable treatment targets within the framework of predictive processing in children and adolescents with FAPDs, and shed light on parental factors that are important for the child’s treatment adherence and effect. Overall, this research can guide the further development of even more effective psychological treatments for one of the most prevalent chronic pain disorders in children and adolescents.

## Abbreviations

BY-GIS: biases in youth toward gastrointestinal-related stimuli
CBT: cognitive behavioral therapy
CPAQ-A8: Chronic Pain Acceptance Questionnaire – Adolescent Short Form
DSQ: daily short questionnaire
FAP-NOS: functional abdominal pain not otherwise specified
FAPD: Functional abdominal pain disorder
FPS-R: Faces Pain Rating Scale – revised
HAPYS: The Health Anxiety by Proxy Scale
HRD: heart rate discrimination
IBS: irritable bowel syndrome
IBS-BRQ: irritable bowel syndrome behavioral response questionnaire
ICBT: internet-delivered cognitive behavioral therapy
ICD-10: International Statistical Classification of Diseases, Tenth Revision
IgA: Immunoglobulin A
PedsQL: Pediatric Quality of Life Inventory
REDCap: Research Electronic Data Capture
SCAS-S: Spence Children Anxiety Scale – Short
SCED: single case experimental design study
SCRIBE: Single-Case Reporting guideline In BEhavioural interventions
SOL: Stop, observe, let go
SPIRIT: Standard Protocol Items Recommendations for Interventional Trials
TSH: thyroid stimulating hormone
VSI: Visceral Sensitivity Index
VSI-C: Visceral Sensitivity Index-Children
